## Abstract

**Introduction:**

Chronic hepatitis B (CHB) is a global public health problem. Antiviral therapy is the primary treatment. Studies have shown that a combined therapy of traditional Chinese medicine (TCM) and conventional antiviral drugs has better efficacy than conventional antiviral for treatment of CHB. *YinQiSanHuang*-antiviral decoction (YQSH) is a TCM compound preparation that has shown an effect on anti-hepatitis B virus and on slowing progression of hepatitis B-related liver diseases. To evaluate the efficacy and safety of YQSH combined with entecavir and its preventive effect on hepatitis B cirrhosis, we designed this randomized, double-blind and placebo-controlled trial. The objective is that the combination of YinQiSanHuang-antiviral decoction with entecavir will reduce the annual incidence of liver fibrosis/cirrhosis to 1%.

**Methods:**

This is a multicenter, randomized, placebo-controlled, double-blinded trial involving five hospitals. A total of 802 patients are randomly allocated to two groups: the YQSH group (*n* = 401) or the placebo group (*n* = 401). The YQSH group receives YQSH with entecavir; the placebo group receives granules of placebo with entecavir. Patients receive treatment for 52 weeks and then are followed up for 52 ± 2 weeks. The primary outcome measure is the annual incidence of cirrhosis. The secondary outcome measures are hepatitis B virus DNA negative rate, hepatitis B surface antigen negative rate, hepatitis B e antigen seroconversion rate, liver function (alanine aminotransferase, aspartate aminotransferase , gamma-glutamyl transferase , alkaline phosphatase , serum albumin, and total bilirubin), spleen thickness, evaluation scores of patients’ clinical symptoms, and safety assessment. Outcomes will be assessed at baseline and after treatment.

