## Background

Chronic hepatitis B (CHB) is a chronic viral infection caused by hepatitis B virus (HBV) and characterized by the persistence of hepatitis B surface antigen (HBsAg) for at least 6 months (with or without concurrent hepatitis B e antigen [HBeAg]). As a global health problem, more than 257 million people worldwide suffer from chronic HBV infection [1, 2]. In 2015, an estimated 887,000 deaths resulted from hepatitis B, mostly from cirrhosis and hepatocellular carcinoma (HCC, i.e., primary liver cancer) [3]; of these CHB is responsible for 30% of all deaths from cirrhosis and 40% of those from HCC [4–6]. China’s prevalence is one of the highest, with about 20 million CHB cases, accounting for 21.5% of the 93 million cases of HBV infection. Without timely testing and treatment, most CHB will develop into cirrhosis, HCC, or finally lead to death [7, 8]. It is estimated that in China there are 20–30 million people with CHB, 1 million with liver cirrhosis, and 0.3 million with HCC caused by hepatitis B [9]. Deaths due to HBV-related liver diseases in China (0.308 million deaths per year) account for more than 30% of the global mortality from HBV (0.887 million deaths per year) [10]. Antiviral therapy is the primary link to slow the conversion of CHB into cirrhosis and can effectively restore liver function and improve survival rate in patients with CHB [11, 12]. Currently, the US Food and Drug Administration (FDA) has approved two types of anti-HBV drugs: interferon (IFN) and nucleos(t)ide analogs (NAs, e.g., entecavir, lamivudine, telbivudine, adefovir, and tenofovir). Although NAs are well tolerated and exhibit an early and potent antiviral effect, the selection of resistant mutants and nephrotoxicity during long-term therapy limit their use [13, 14].

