Chinese herbal medicine (CHM) is one of the most popular complementary and alternative therapies for CHB, and numerous studies have reported its anti-HBV effect. CHMs have two major characteristics: (1) they are flexible and adaptable in various kinds of herbal medicines, with complex compositions, which means they do not easily cause drug resistance; (2) they are taken from the natural environment, using rich, easily obtainable sources. CHMs are generally well tolerated for long-term treatment, which provides a good therapeutic effect in the prevention and treatment of CHB. A cohort study showed that the use of CHM is associated with significantly reversed cirrhosis and reduced HCC risk in patients with CHB [15]. Many studies have identified active ingredients in single herbs or in herbal formulas that have therapeutic effects on CHB, with associated anti-HBV, antifibrosis, liver protection, antitumor, antibacterial, antioxidant, anti-acute liver injury, and anti-HCC mechanisms [16–21]. An ideal anti-HBV drug should have good safety, good drug resistance, long-lasting effects, and no withdrawal rebound, and be able to stimulate host immune responses and effectively inhibit virus replication or even eliminate the virus [22, 23]. Studies have identified that CHM not only has antiviral effects, but it also can enhance the body’s immunity to improve its antiviral ability. For example, an extract of *Le-Cao-Shi*, which is a kind of TCM herb, can restrain the expression of duck hepatitis B model surface antigen (DHBsAg), hepatitis B e antigen (DHBeAg), and HBV DNA (DHBV DNA), correspondingly, in a HepG2.2.15 cellular model, and could also significantly inhibit the secretions of HBsAg and HBeAg [24]. Results from another study demonstrated that cordycepin, which is extracted from TCM, could work as an adjuvant to the hepatitis B vaccine, and this type of new vaccine simultaneously improves the humoral and cellular immunity of BALB/c mice without side effects [25]. *YinQiSanHuang*-antiviral decoction (YQSH) is a CHM formula that has been used for more than 30 years for CHB treatment. It has shown effects on anti-HBV DNA and increasing the level of alanine aminotransferase (ALT) in a small-scale clinical study [26]. Research results suggested that YQSH not only enhances the antiviral effect of entecavir, but also has a significant preventive effect on CHB-related cirrhosis. Thus, we designed this study and have set the objective as “the combination of YQSH with entecavir will reduce the annual incidence of liver fibrosis/cirrhosis to 1%” to test the effectiveness of this combination.

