### Eligibility criteria

#### Inclusion criteria

The inclusion criteria are as follows: (1) patients who have a history of hepatitis B infection or HBsAg positive for more than 6 months, and their current HBsAg and/or HBV DNA levels are still positive; (2) patients who meet the criteria for antiviral indications in the “Asian-Pacific consensus statement on the management of CHB: a 2008 update” [27]; patients taking entecavir dispersible tablets may also be included. (This study will enroll patients who have taken entecavir previously; conversely, patients who have taken immune stimulatory drugs or other antiviral drugs within 3 months will not be enrolled.); (3) patients between 18 to 65 years old; (4) patients showing syndromes of liver stagnation and spleen deficiency and dampness in TCM. For the TCM diagnostic criteria, we refer to “National Standards for TCM Clinical Diagnosis and Treatment in the People’s Republic of China” [28] and the “Medical Consensus of diagnosis and treatment of cirrhosis with integrated TCM and Western medicine” [29], published by the Digestive System Diseases Committee, Society of Integrated Traditional Chinese and Western Medicine.

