### Interventions

#### Description

All patients will have a screening test during the screening period in clinic if they meet the inclusion criteria. The screening evaluation includes the patient’s general status, disease-related symptoms and signs, and corresponding laboratory tests, including the following: urine pregnancy test (women of childbearing age), HBV DNA, liver function, FibroScan, liver B-mode ultrasound or magnetic resonance imaging (MRI)/computed tomography (CT), and other examinations. The test group (YQSH group) will receive YQSH formula granules 5 g (first brewed with 150–200 ml water) twice a day, combined with entecavir 0.5 mg once a day. The control group (placebo group) will receive YQSH placebo formula granules 5 g (first brewed with 150–200 ml water) twice a day, combined with entecavir 0.5 mg once a day. The entecavir was produced by ChiaTai TianQing Pharmaceuticals in Jiangsu, China (production batch number H20100019). The main components of YQSH, totaling 14 kinds of herbs, are shown in Table 1. The test drugs are made into Chinese medicine formula granules. Before taking YQSH, the mixed formula granules are boiled with 150–200 ml water for 3–5 min. The YQSH placebo is made of excipients, thinners, coloring agents, flavoring agents, and fried malt, and is similar to YQSH in shape, color, smell, and taste.

**Table 1 Tab1:** Main components of *YinQiSanHuang*-antiviral decoction

Chinese name	Latin name	English name	Pharmacological action	Main active ingredient	Original producing area	Medicinal part	Dosage (g)
*Huang Qi*	*Astragalus propinquus* Schischkin	Radix Astragali	Promotes liver cell growth, anti-liver fibrosis, antiviral, regulates immunity	Astragaloside (I,V, III), calycosin	Neimenggu, China	Rhizome	12
*Yin Chen*	*Artemisia capillaris* Thunb.	Virgate wormwood herb, capillary wormwood herb	Lowers blood lipids to treat fatty liver, reduces alcoholic liver damage, inhibits the replication of hepatitis B virus DNA	Capillin, capillene, capillanol, capillarisin, 6, 7-dimethylsculetin	Shanxi, China	Aboveground part of the plant	12
*Huang Qin*	*Scutellaria baicalensis* Georgi	Baical skullcap root	Anti-hepatocyte inflammation, anti-hepatocyte apoptosis, anti-hepatocyte mitochondrial lipid peroxidation, regulates immunity	Baicalein, neobaicalein, skullcap flavone II, baicalin, wogonin	Hebei, China	Rhizome	3

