#### Secondary outcomes

The secondary outcomes include HBV DNA negative rate, HBsAg negative rate, HBeAg seroconversion rate, liver function (ALT, aspartate aminotransferase [AST], gamma-glutamyl transferase [GGT], alkaline phosphatase [ALP], serum albumin [ALB], and total bilirubin [TBIL]), spleen thickness, and the evaluation scores of patients’ clinical symptoms.

These indicators are observed before the treatment, at 26 weeks of treatment, at 52 weeks of treatment, at the 26 ± 2 weeks follow-up period, and at the 52 ± 2 weeks follow-up period.

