### Statistics

#### Outcomes

For the statistical analysis comparing the primary outcome incidence between the two groups, we will use the χ^2^ test and set *P* < 0.05 (95% confidence interval) as statistically significant. For the secondary outcomes, the measurement data are expressed as mean ± standard deviation, the count data are expressed as frequency and percentage (*f*, %), and the frequency or percentage of the efficacy evaluation index is converted into frequency and percentage (*f*, %). For comparison of the mean between the two groups, the homogeneity test is performed first. If the variances are equal, the *t* test is used. If the variances are unequal, the non-parametric *t* test is used. The measurement data of each group before and after treatment are compared using the paired *t* and/or *t* test. The comparison of grid table count data will be performed using the χ^2^ test, and the comparison of rank data will use the rank sum test. *P* < 0.05 will be used as the statistical difference. The data analysis will be performed using SPSS 19.0 statistical software.

The baseline is defined as the last observation data before the first medication, which includes demographic characteristics and clinical baseline data: age, sex, vital signs (height, weight, temperature, heart rate, blood pressure, breathing), clinical symptom scores, HBV DNA, liver stiffness (FibroScan/Fibrotouch), entecavir treatment history, and CHB-related diseases.

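### HBV DNA is tested only as a yes/no negative rate without baseline adjustment, which gives up some precision that data already being collected could supply

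*Protocol article*

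**What the plan says.** All references are to the protocol article.

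- **Outcome form.** The Abstract (Methods) says "The secondary outcome measures are hepatitis B virus DNA negative rate". The Secondary outcomes section repeats it: "The secondary outcomes include HBV DNA negative rate, HBsAg negative rate, HBeAg seroconversion rate". No quantitative HBV DNA outcome is listed.
- **Timing.** "These indicators are observed before the treatment, at 26 weeks of treatment, at 52 weeks of treatment", and then at two follow-up visits.
- **Test.** Statistics, Outcomes, assigns a χ² test to count data and names no adjustment for baseline.
- **Baseline.** The same section counts among the baseline data "clinical symptom scores, HBV DNA, liver stiffness (FibroScan/Fibrotouch), entecavir treatment history".
- **Background treatment.** Under Interventions, Description, each arm's granules are "combined with entecavir 0.5 mg once a day". The Background describes the class thus: "Although NAs are well tolerated and exhibit an early and potent antiviral effect".
- **Rationale.** The Background reports earlier research suggesting that "YQSH not only enhances the antiviral effect of entecavir".
- **Entry.** Patients qualify if "their current HBsAg and/or HBV DNA levels are still positive", and prior entecavir users may enter. A patient who is already HBV DNA negative can therefore be enrolled.

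**The concern.** Whether the formula adds antiviral effect to entecavir is the main mechanistic question behind the trial. For HBV DNA it is answered by a single cut at the assay limit. That cut drops the size of the decline, and the χ² test ignores how far each patient had to fall, although baseline level strongly predicts who becomes negative. ALT, AST and the other liver tests are listed as measurements, to which the Statistics section gives mean comparisons. HBV DNA is the quantitative virological marker reduced to yes/no.

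What is at stake is the precision of a secondary outcome. If a modest added effect exists, the planned test is less likely to show it than an analysis of the same samples that uses the baseline and the level.

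**Working it through.** **The plan's own figure.** The only sample size in the article is for cirrhosis, and it reproduces: (1.96 + 1.282)² / [2(sin⁻¹√0.01 − sin⁻¹√0.05)²] = 334.5 per group, and 334 × 1.2 × 2 = 801.6, about 802. It says nothing about HBV DNA. The article gives no expected negative rate, assay limit, SD, effect size or share of patients detectable at baseline, so everything below rests on assumed inputs.

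**Simulation.** Assumptions: 150 baseline-detectable patients per arm; baseline SD 1.5 log10; slope on baseline 0.6; residual SD 1.2 log10, normal; assay limit 20 IU/mL; true extra reduction 0.4 log10; two-sided 5%. The control mean is set to give each negative rate. There were 1,000 runs per setting, so the Monte Carlo standard error is at most √(0.5 × 0.5/1000) = 1.6 points.

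| Control negative rate | χ² (planned) | Logistic + baseline | Tobit, no baseline | Tobit + baseline |
|---|---|---|---|---|
| 50% | 50% | 59% | 57% | 71% |
| 60% | 44% | 51% | 51% | 63% |
| 75% | 39% | 45% | 43% | 53% |
| 90% | 22% | 27% | 24% | 28% |

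Type I error of the χ² test and the adjusted Tobit model was 4.6–6.6% (500 null runs each).

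**Power converted to information.** Information is proportional to (1.96 + z)², where z is the normal quantile of the power.

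- 50% negative: χ² (1.96 + 0.00)² = 3.84; adjusted Tobit (1.96 + 0.553)² = 6.32; ratio 0.61.
- 60%: 3.27 / 5.25 = 0.62.
- 75%: 2.83 / 4.14 = 0.68.
- 90%: 1.41 / 1.90 = 0.74.

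To match the adjusted censored model, the planned test would need 1/0.74 − 1 = 35% to 1/0.61 − 1 = 64% more patients.

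**Where the gain comes from.** The adjusted logistic model has information 4.79, 3.94, 3.37 and 1.81 in the four settings.

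- Baseline adjustment alone (χ² over logistic): 0.80, 0.83, 0.84, 0.78.
- Keeping the quantity (logistic over Tobit): 0.76, 0.75, 0.81, 0.96.

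Both parts matter at 50–75% negative. At 90% nearly all of the gain is baseline adjustment.

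**Analytic check without baseline.** Take a normal latent log10 level, negative rate p and c = Φ⁻¹(p). The binary outcome carries φ(c)²/[p(1 − p)] of the uncensored information. A left-censored analysis carries φ(c)²/p + ∫ x²φ(x)dx from c upward. At p = 0.5 this is 0.637 against 0.818, so the binary outcome keeps 78%. At p = 0.9 it is 0.342 against 0.359, or 95%. The further values are 88% at p = 0.7, 92% at 0.8 and 97% at 0.95. When most patients are below the limit there is little quantity left to use.

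**Population.** Suppose conversion among detectable patients is 70% against 80%, with 401 per arm. With none already negative at entry, power is 91%. With half already negative it is 57% if all patients are analysed and 64% if only detectable patients are. With 70% already negative it is 36% and 43%.

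**The case against.** Several objections stand.

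- A reader might infer that the yes/no cut throws away most of the information. It does not: the planned test keeps about 60–75% in every setting above. More than half is lost only against uncensored values at negative rates of about 80% or more, and such values do not exist for patients below the assay limit.
- A reader might infer from entecavir's potency that the test runs near a ceiling. That is plausible, more so because pretreated patients may enter, but the article states no negative rate. Near a ceiling, keeping the quantity also helps least.
- A reader might conclude that a real effect will probably be reported as no difference. That depends on the 150 per arm. Multiplying (1.96 + z) by √(401/150) = 1.635 gives χ² power of about 89%, 84%, 78% and 49% if all 401 per arm were detectable at baseline. The adjusted Tobit model would then have about 98%, 96%, 91% and 61%.
- The simulated data follow the model that Tobit assumes. With heavier-tailed (t, 4 df) errors, Tobit's advantage over adjusted logistic largely disappears. The gain from baseline adjustment mostly remains at 50–75% negative.
- HBsAg negative rate and HBeAg seroconversion also address antiviral effect. The negative rate itself is clinically standard and fits the Discussion's view of long-term HBV DNA inhibition as a surrogate, so it need not be demoted to a descriptive figure.

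It can also be said that covariate adjustment is usually left to an analysis plan, which is not shown here. That plan may indeed add it. But the article does fix the outcome as a rate and the test as χ², and that choice can be assessed as written.

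**Conclusion.** The point holds as a moderate loss of precision on a secondary outcome. HBV DNA is compared only as a proportion, without baseline adjustment, although the baseline level is recorded and later values are observed. Under the stated assumptions the planned test has about 60–75% of the information of a baseline-adjusted censored analysis. Part of the gain comes from adjustment. The rest comes from keeping the quantity, mainly at moderate negative rates, most likely at week 26, and hardly at all at 90% or above.

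The figures depend on the assumed SDs, slope, effect, assay limit and number detectable at baseline, and on normal errors. The documents do not support a claim that most information is lost, that a ceiling is established, or that a null result is likely. The conclusion on cirrhosis is unaffected.

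**What to change.** Amend the Secondary outcomes section and Statistics, Outcomes, for patients with detectable HBV DNA at baseline:

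1. Keep the HBV DNA negative rate as a tested secondary outcome, but compare arms with a model that adjusts for baseline log10 HBV DNA, for example logistic regression.
2. Add log10 HBV DNA at weeks 26 and 52 as a supportive secondary outcome. Model it on arm and baseline level, treat values below the assay limit as left-censored (not as zero or as the limit), and report the difference in log10 IU/mL with its 95% CI.

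This costs about a paragraph of text and needs no new visit, sample or patient. It assumes that the assay reports a level at each visit, as the inclusion criteria's reference to HBV DNA levels suggests. The downsides are slightly more analysis work, software beyond the basic SPSS menus, and a Tobit model that leans on normality when most values are censored. That last limitation is why the quantitative analysis should be supportive and the adjusted negative rate should stay.

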**Discussion:**

Combination therapy could become a trend for treatment of CHB, and this trial expects to provide credible clinical evidence for the future combination of TCM and conventional antiviral drugs for the treatment of CHB.

**Trial registration:**

Chinese Clinical Trial Registry: ChiCTR1900021521. Registered on 25 February 2019.

## Background

Chronic hepatitis B (CHB) is a chronic viral infection caused by hepatitis B virus (HBV) and characterized by the persistence of hepatitis B surface antigen (HBsAg) for at least 6 months (with or without concurrent hepatitis B e antigen [HBeAg]). As a global health problem, more than 257 million people worldwide suffer from chronic HBV infection [1, 2]. In 2015, an estimated 887,000 deaths resulted from hepatitis B, mostly from cirrhosis and hepatocellular carcinoma (HCC, i.e., primary liver cancer) [3]; of these CHB is responsible for 30% of all deaths from cirrhosis and 40% of those from HCC [4–6]. China’s prevalence is one of the highest, with about 20 million CHB cases, accounting for 21.5% of the 93 million cases of HBV infection. Without timely testing and treatment, most CHB will develop into cirrhosis, HCC, or finally lead to death [7, 8]. It is estimated that in China there are 20–30 million people with CHB, 1 million with liver cirrhosis, and 0.3 million with HCC caused by hepatitis B [9]. Deaths due to HBV-related liver diseases in China (0.308 million deaths per year) account for more than 30% of the global mortality from HBV (0.887 million deaths per year) [10]. Antiviral therapy is the primary link to slow the conversion of CHB into cirrhosis and can effectively restore liver function and improve survival rate in patients with CHB [11, 12]. Currently, the US Food and Drug Administration (FDA) has approved two types of anti-HBV drugs: interferon (IFN) and nucleos(t)ide analogs (NAs, e.g., entecavir, lamivudine, telbivudine, adefovir, and tenofovir). Although NAs are well tolerated and exhibit an early and potent antiviral effect, the selection of resistant mutants and nephrotoxicity during long-term therapy limit their use [13, 14].

Chinese herbal medicine (CHM) is one of the most popular complementary and alternative therapies for CHB, and numerous studies have reported its anti-HBV effect. CHMs have two major characteristics: (1) they are flexible and adaptable in various kinds of herbal medicines, with complex compositions, which means they do not easily cause drug resistance; (2) they are taken from the natural environment, using rich, easily obtainable sources. CHMs are generally well tolerated for long-term treatment, which provides a good therapeutic effect in the prevention and treatment of CHB. A cohort study showed that the use of CHM is associated with significantly reversed cirrhosis and reduced HCC risk in patients with CHB [15]. Many studies have identified active ingredients in single herbs or in herbal formulas that have therapeutic effects on CHB, with associated anti-HBV, antifibrosis, liver protection, antitumor, antibacterial, antioxidant, anti-acute liver injury, and anti-HCC mechanisms [16–21]. An ideal anti-HBV drug should have good safety, good drug resistance, long-lasting effects, and no withdrawal rebound, and be able to stimulate host immune responses and effectively inhibit virus replication or even eliminate the virus [22, 23]. Studies have identified that CHM not only has antiviral effects, but it also can enhance the body’s immunity to improve its antiviral ability. For example, an extract of *Le-Cao-Shi*, which is a kind of TCM herb, can restrain the expression of duck hepatitis B model surface antigen (DHBsAg), hepatitis B e antigen (DHBeAg), and HBV DNA (DHBV DNA), correspondingly, in a HepG2.2.15 cellular model, and could also significantly inhibit the secretions of HBsAg and HBeAg [24]. Results from another study demonstrated that cordycepin, which is extracted from TCM, could work as an adjuvant to the hepatitis B vaccine, and this type of new vaccine simultaneously improves the humoral and cellular immunity of BALB/c mice without side effects [25]. *YinQiSanHuang*-antiviral decoction (YQSH) is a CHM formula that has been used for more than 30 years for CHB treatment. It has shown effects on anti-HBV DNA and increasing the level of alanine aminotransferase (ALT) in a small-scale clinical study [26]. Research results suggested that YQSH not only enhances the antiviral effect of entecavir, but also has a significant preventive effect on CHB-related cirrhosis. Thus, we designed this study and have set the objective as “the combination of YQSH with entecavir will reduce the annual incidence of liver fibrosis/cirrhosis to 1%” to test the effectiveness of this combination.
